
#### Validation phase

Clinical software validation (Aim 2)

After screening of eligible patients written informed consent will be obtained from parents or caregivers.

Clinical screening will be performed as mandated by the Italian law. Pre-ductal (right arm) oxygen saturation and post-ductal (leg) oxygen saturation will be recorded. Physical examination will include femoral arterial pulse detection and face-to-face heart auscultation.

Clinical screening output threshold criteria is summarized in *Table 2*.

**Table 2 ztag103-T2:** Clinical screening output threshold criteria

	Positive screening	Negative screening
**Oxygen saturation**	<95% and/or arm-to-leg difference >5%	>95% and arm to leg difference < 5%
**Femoral arterial pulse**	Absent or reduced	Normal
**Heart auscultation**	Any divergence from normal cardiac auscultation	Normal I/II heart sound, venous hum, physiologic murmur

For this phase we will enrol patients using a block stratification for high SHD risk vs. low (standard) SHD risk status for each newborn.

Heart recordings will be acquired (15 s length) before comprehensive echocardiography by a trained research investigator. Age at recording and echocardiographic evaluation will be planned not before 7 days of post-natal life to allow completion of proper cardio-circulatory transition in the healthy newborns (i.e. ductal closure, pulmonary vascular remodelling, foramen ovale physiologic shunt).

The echocardiography will be performed according to current guidelines by expert paediatric cardiovascular imager blinded to clinical and digital screening results. Preliminary inter- and intra-observer variability between dedicated expert cardiovascular imagers among centres will be performed in small patient subset.

Pertinent anonymized demographics, cardiovascular status, and pertinent research variables will be stored in an encrypted, web-based, research-focused online software.

Digitally anonymized echocardiographic clips will be transferred to the Echocardiography Study Core Lab who will perform the final, formal reading of the exams dichotomizing patient population into normal and abnormal examination. Any potential conflict of interpretation will be solved with consensus and among all Units cardiac imagers.

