**Figure 1 ztag103-F1:**
[figure not shown]
Diagram of validation phase. Each newborn with blinded cardiovascular status will undergo clinical screening as indicated by current practice and regulations and digital screening using the DI_SOUND algorithm. Gold standard evaluation will be comprehensive echocardiography. Pertinent diagnostics are reported at the bottom.

Cost-effectiveness validation (Aim 3)

Aim 3 will evaluate the potential impact of digital screening on healthcare utilization and costs compared with current standard clinical screening. The target population will consist of newborns at low risk for SHD, with no prior indication for cardiovascular examination, in order to approximate the prevalence of undiagnosed cardiovascular abnormalities in the general newborn population.

For the purpose of this analysis, outcomes will be explicitly defined as follows:

Prevented unnecessary examinations: cases in which (healthy) newborns with a positive result at standard clinical screening but a negative result at digital screening are subsequently confirmed to be free of SHD (i.e. false positives avoided by digital screening).Missed necessary examinations: cases in which newborns (with SHD) with a positive result at standard clinical screening but a negative result at digital screening are subsequently diagnosed with SHD (i.e. false negatives introduced by digital screening).

A decision-analytic modelling framework will be developed to compare digital screening with standard clinical practice. Model inputs will include estimates of SHD prevalence, test performance characteristics (sensitivity and specificity of both screening strategies), and downstream diagnostic pathways. Cost estimates will be derived from national diagnosis-related group reimbursement schedules to reflect healthcare system expenditures associated with confirmatory examinations and missed diagnoses.

To account for parameter uncertainty and variability, a probabilistic sensitivity analysis will be conducted using Monte Carlo simulation. This approach will allow repeated sampling from predefined distributions of key parameters (e.g. prevalence, sensitivity, specificity, and costs) to generate distributions of expected costs and outcomes for each screening strategy. The primary outcome will be the incremental cost-effectiveness of digital screening compared with standard clinical screening, expressed in terms of cost per unnecessary examination avoided and cost per missed SHD case.

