## Discussion

The DI_SOUND study is designed to develop and validate a digital classifier of neonatal cardiac sounds with the aim of improving the efficiency and effectiveness of screening for SHD in newborns. Current neonatal cardiovascular screening strategies rely on pulse oximetry (pre- and post-ductal oxygen saturation) combined with physical examination prior to discharge.^12–16^ While this approach has improved early detection of critical congenital heart disease, its diagnostic performance remains suboptimal, particularly in terms of sensitivity and operator dependency.^16^

Cardiovascular auscultation, historically a cornerstone of neonatal assessment, is inherently subjective and dependent on clinician experience.^14^ Several contemporary factors further limit its effectiveness. First, increasing prenatal detection of SHD has led to centralization of care, reducing exposure of general paediatric trainees and frontline providers to pathological cardiac findings, thereby potentially diminishing auscultatory proficiency.^35^ Second, early postnatal discharge (typically within 48–72 h) may occur before the full haemodynamic expression of certain defects, particularly those involving post-tricuspid shunts, due to persistently elevated pulmonary vascular resistance during transitional circulation. Third, the growing reliance on advanced diagnostic technologies may paradoxically reduce emphasis on meticulous physical examination skills.^35^ Collectively, these factors contribute to the persistence of false-negative screening results, which carry significant clinical risk.

Conversely, current screening strategies are also limited by suboptimal specificity, leading to a considerable number of false-positive cases. This results in unnecessary cardiology referrals, increased healthcare utilization, prolonged hospitalization, and heightened parental anxiety. Therefore, there is a clear unmet need for tools that can enhance both sensitivity and specificity while remaining accessible and scalable.

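### Aim 3 prices only downstream events, so the cost of delivering either screen is absent from an incremental cost-effectiveness outcome

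*Protocol article*

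**What the plan says.** The section on cost-effectiveness validation (Aim 3) defines the outcome: "The primary outcome will be the incremental cost-effectiveness of digital screening compared with standard clinical screening". Two ratios are to be reported for it, since it is "expressed in terms of cost per unnecessary examination avoided and cost per missed SHD case".

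It then says what goes into the model. On inputs: "Model inputs will include estimates of SHD prevalence, test performance characteristics (sensitivity and specificity of both screening strategies), and downstream diagnostic pathways". On costs: "Cost estimates will be derived from national diagnosis-related group reimbursement schedules to reflect healthcare system expenditures associated with confirmatory examinations and missed diagnoses". The Monte Carlo analysis is described as "repeated sampling from predefined distributions of key parameters (e.g. prevalence, sensitivity, specificity, and costs", with no further definition of the costs that are sampled.

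Three other places bear on how the two screens relate:

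- The Validation phase section (under Study procedure) says: "Clinical screening will be performed as mandated by the Italian law". The Figure 1 legend has every newborn undergo both screens.
- The Discussion presents the classifier as a complement to existing screening and not as a substitute for it.
- The Aim 3 outcome definitions count an examination as prevented when a healthy newborn is positive on clinical screening and negative on digital screening. There the digital result overrides the clinical one.

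**The concern.** An incremental cost compares the full cost of two strategies. The digital strategy uses an electronic stethoscope, software, a data platform and a trained operator, and some recordings will have to be repeated. None of these appears in the cost scope or among the model inputs, and the cost of delivering clinical screening is not there either. The article is not merely silent on costs. It names a source and a scope, and that scope does not match the outcome.

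The delivery cost falls on every newborn, while the counted savings arise in only a few per cent of them. A small cost per newborn can therefore outweigh a saving on examinations. The Monte Carlo analysis cannot reveal this, because it varies only parameters that are in the model. The study's stated aims include lower health-care cost, and a comparison in which the tested product is free cannot support that claim.

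**Working it through.** The article gives no unit cost and no cost-effectiveness ratio, so there is no figure of its own to reproduce. The check uses expected counts per 1,000 low-risk newborns.

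**Inputs**

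- Prevalence 1% (Statistic plan, Aim 2 sample size): 10 affected, 990 healthy.
- Clinical screening: specificity 95–99%, sensitivity 70–80% (Limitation).
- Digital screening: targets above 95% sensitivity and above 90% specificity (Statistic plan, Aim 1), taken here as 95% and 90%.
- Not in the documents, so kept as symbols: c = delivery cost of one digital screen, k = delivery cost of one clinical screen, E = cost of one confirmatory examination, M = cost of one missed case.

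**1. Omitted term if digital is an add-on.** 1,000 × c = 1000c per 1,000 newborns.

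**2. Ceiling on prevented unnecessary examinations.** Only clinical false positives can be prevented: 990 × (1 − specificity).

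- Specificity 95%: 990 × 0.05 = 49.5.
- Specificity 99%: 990 × 0.01 = 9.9.

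This is generous to digital screening, because it ignores the false positives that digital itself adds among clinical negatives.

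**3. Break-even on examination cost alone.** The saving is at most 49.5E or 9.9E. It is cancelled when 1000c exceeds it:

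- c/E > 49.5/1,000 = 4.95%, or c/E > 9.9/1,000 = 0.99%.
- Per examination avoided, the omitted cost is 1,000/49.5 = 20c to 1,000/9.9 = 101c.

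**4. Range of assumed c/E.** Net examination cost per 1,000 = 1000c − saving, in units of E:

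| c/E (assumed) | clinical specificity 95% | clinical specificity 99% |
|---|---|---|
| 0 (as the plan is written) | −49.5 | −9.9 |
| 0.01 | 10 − 49.5 = −39.5 | 10 − 9.9 = +0.1 |
| 0.05 | 50 − 49.5 = +0.5 | 50 − 9.9 = +40.1 |
| 0.10 | 100 − 49.5 = +50.5 | 100 − 9.9 = +90.1 |
| 0.50 | 500 − 49.5 = +450.5 | 500 − 9.9 = +490.1 |

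**5. Missed cases, which the plan does count.** If the digital result decides referral, fewer cases are missed: 10 × (0.95 − 0.80) = 1.5 to 10 × (0.95 − 0.70) = 2.5 per 1,000. These savings alone offset 1000c if M exceeds 1000c/2.5 = 400c to 1000c/1.5 = 667c. The documents give no M, so the sign of the total cannot be settled.

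**6. Digital specificity at and above its floor.**

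- At 90%, digital gives 990 × 0.10 = 99 false positives. That is 99 − 49.5 = 49.5 to 99 − 9.9 = 89.1 more than clinical screening. The examination cost is then already against digital, and adding c does not change its sign.
- At 99% against a clinical 95%, false positives fall by 49.5 − 9.9 = 39.6. Subtracting the 1.5–2.5 extra true-positive examinations leaves 38.1–37.1 fewer examinations, so the break-even c/E is about 3.7–3.8%.

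**7. If digital replaces clinical screening.** Both delivery costs are missing, and the omitted term is 1000(c − k). Its sign is unknown from the documents.

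**The case against.** The strongest reply is that the lists are open. The inputs are said to include certain items, the Monte Carlo parameters are given as examples with costs unrestricted, and a full protocol sits in a supplement that is not shown. A unit-cost list is the sort of detail an article leaves out. This limits certainty: the finding describes the text at hand. It does not remove the point, because the article does state a cost source and a scope, and both stop downstream of the screen.

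The second reply is that the add-on framing is not settled. The legal mandate and the Discussion point to an add-on, but the Aim 3 outcome definitions let a negative digital result override a positive clinical one, which fits replacement as well. This stands. Under replacement the bias is a difference that could go either way, and a correction that charges only the digital arm could itself bias the comparison.

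A reader might infer more than the documents support in two respects:

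- **That the Aim 3 conclusion would reverse.** At the 90% specificity floor the examination cost is already unfavourable to digital, and the plan counts savings from fewer missed cases. Reversal is possible in some scenarios but is not shown.
- **That an extra visit belongs in the omitted cost.** The Validation phase section says "Age at recording and echocardiographic evaluation will be planned not before 7 days of post-natal life", and the Discussion puts typical discharge at 48–72 h. That timing governs the study's recording and reference echocardiogram together. Nothing says that routine use would need a separate visit.

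**Conclusion.** The concern holds in a conditional form. As written, the Aim 3 cost scope leaves out the delivery cost of both screens, which does not fit an incremental cost-effectiveness outcome.

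- **Add-on:** the incremental cost is understated by 1000c per 1,000 newborns, which favours digital screening. The largest possible examination saving disappears once c passes about 1–5% of one confirmatory examination. This rests on 1% prevalence and 95–99% clinical specificity, both from the article, and on no assumed price.
- **Replacement:** the bias is 1000(c − k) per 1,000, of unknown sign.

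The documents do not support a monetary size for the error or a statement that the overall result changes sign, since c, k, E and M are all absent. The bias is on the cost side only and does not mean that digital screening will look favourable overall. Confidence is medium because the supplement is not shown. Aims 1 and 2 are unaffected. The plan should be changed before the model is built.

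**What to change.** - State whether the modelled strategy adds digital screening to clinical screening or replaces it, and how discordant results are handled in the model.
- Enter a delivery cost per newborn for each screen (device spread over its working life, software, staff time, repeat recordings), taken from purchase and staffing records.
- Give these inputs distributions in the Monte Carlo analysis.
- Keep reimbursement tariffs for confirmatory examinations and missed diagnoses.
- Treat a separate recording visit as a scenario only, not as part of the base case.

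The cost is one or two more inputs, with no new patients and no change to the design. The downside is that the result may be less favourable to digital screening.

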## Limitation

The most notable limitation is the absence of reliable data to calculate power for the development/training phase. Second, some severe SHD (among others transposition of the great arteries with intact ventricular septum) may have minimal acoustic correlates, and, therefore, our approach may be of limited efficiency for these lesions. Third, clinical screening modality integrates a variety of non-acoustic information, such as general newborn appearance, breathing pattern, femoral pulses, oxygen saturation. It is possible that clinical screening method may outperform digital screening for specific subsets of congenital lesions. Fourth, the frequency response of the digital stethoscope may change significantly between stethoscope models, and this may affect the ability of the classifier to transfer performance to a different model. To mitigate this aspect, we have decided to disable all digital filtering and equalization upon sound acquisition. Development and validation of diagnostic tool in a specific world region may constitute *per se* a limit affecting world-wide generalizability. Lastly, small/premature neonates (<1.5 kg) were not included in the target population of our study by design. This neonatal population routinely undergoes comprehensive cardiovascular evaluation, including echocardiographic screening, which reduces the potential added value of a digital heart sound–based screening tool in this subgroup. They frequently present with clinical and physiological conditions (such as mechanical ventilation, underlying lung disease, haemodynamically significant patent ductus arteriosus, and pulmonary vascular abnormalities) that may introduce substantial acoustic variability and confound heart sound recordings. These factors would limit both the reliability of data acquisition and the generalizability of a classifier intended for the broader neonatal population. Fifth, we are aware that a specificity of 90% may be considered lower than expected for a screening test, however, few consideration should be made to this regard: (i) specificity for current clinical screening modality is reported to be between 95% and 99% with a much lower sensitivity (70–80%) and (ii) our boundary condition is assumed under worst case scenario but we aim for a significantly higher specificity and in the Supplementary material online, *Table S3* of the Online Supplementary Material we are reporting a summary table for diagnostic performance of our classifier under different scenarios showing a sustainable workload for lower specificity compared with optimal specificity (about 80 false-positive newborns every/1000). Finally, given the clinical fragility of preterm infants, we carefully considered the ethical implications of additional handling and sensor application and examination, including potential risks of infection and discomfort.

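### Aim 3 defines its outcomes as one-directional counts but makes two incremental ratios primary; on either reading the result can point the wrong way

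*Protocol article*

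**What the plan says.** All of this stands in the protocol article, in the part on cost-effectiveness validation (Aim 3), unless another section is named.

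- **Primary outcome.** Digital screening is compared with standard clinical screening by an incremental cost-effectiveness measure, given as two ratios: "expressed in terms of cost per unnecessary examination avoided and cost per missed SHD case".
- **Outcome definitions.** Prevented unnecessary examinations are healthy newborns who are positive on clinical and negative on digital screening ("i.e. false positives avoided by digital screening"). Missed necessary examinations are newborns with SHD who show the same pattern ("i.e. false negatives introduced by digital screening"). The opposite pattern, clinical negative and digital positive, enters neither definition.
- **Model inputs.** These include prevalence and "test performance characteristics (sensitivity and specificity of both screening strategies").
- **Uncertainty.** The plan states that "a probabilistic sensitivity analysis will be conducted using Monte Carlo simulation", and that repeated sampling serves "to generate distributions of expected costs and outcomes for each screening strategy".
- **Expected performance.** The Statistic plan aims for digital sensitivity above 95% and specificity above 90%; the Aim 2 sample size uses a sensitivity of about 90%. The Limitation section says that "specificity for current clinical screening modality is reported to be between 95% and 99" per cent, with sensitivity of 70–80%. It calls the 90% digital specificity a worst case and hopes for a clearly higher value.

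**The concern.** The definitions and the primary outcome do not describe the same quantity. The definitions take one discordant cell among healthy newborns and one among newborns with SHD, so they can be zero but never negative. An incremental comparison built from each strategy's sensitivity and specificity gives the difference between two strategies, which can take either sign. The section does not say which one is the denominator.

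Both readings cause trouble. The one-directional count credits digital screening with what it avoids among healthy newborns and ignores what it adds; among newborns with SHD it does the reverse. The net increment gives a ratio whose sign does not reveal which strategy is better. The second ratio also has a harm, the missed case, as its denominator. Nothing in the two ratios weighs unnecessary examinations against missed disease, which is the choice a screening programme faces. At stake is the direction in which the headline result of Aim 3 is read.

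**Working it through.** **Inputs**

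- Prevalence 1% (Statistic plan, Aim 2): 990 healthy newborns and 10 with SHD per 1,000. Aim 3 targets low-risk newborns, for whom no separate figure is given, so 1% is an assumption there.
- Digital specificity 90%; digital sensitivity 90% or 95% (Statistic plan).
- Clinical specificity 95–99%, sensitivity 70–80% (Limitation).
- 1,900 × 0.01 = 19 SHD cases in the validation cohort.
- Conditional independence of the two screens given disease status: an assumption, needed for the literal reading only.

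**The plan's own figure.** Aim 3 states no number. The nearest is the Limitation section's figure of about 80 false positives per 1,000. At 90% specificity the absolute number is 990 × 0.10 = 99. As an excess over a 98% specificity it is 990 × 0.08 = 79.2. The supplementary table behind it is not at hand, so I neither confirm nor fault it, and nothing below depends on it.

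**Literal reading, healthy newborns, per 1,000**

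| Clinical specificity | Credited as prevented: 990 × (1 − spec_clin) × 0.90 | Introduced, not counted: 990 × spec_clin × 0.10 | Net |
|---|---|---|---|
| 95% | 44.55 | 94.05 | −49.5 |
| 97% | 26.73 | 96.03 | −69.3 |
| 99% | 8.91 | 98.01 | −89.1 |

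The net column does not depend on the independence assumption, but the credited column does. At 95% clinical specificity it runs from 0 (every clinical false positive is also a digital one) to 990 × 0.05 = 49.5 (no overlap). Sensitivity and specificity alone therefore do not determine the count that the section defines.

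**Literal reading, 19 newborns with SHD**

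- Counted as missed, 19 × sens_clin × (1 − sens_dig): from 19 × 0.70 × 0.05 = 0.67 to 19 × 0.80 × 0.10 = 1.52.
- Chance that this count is zero, (1 − p)^19: from (1 − 0.08)^19 = 0.205 to (1 − 0.035)^19 = 0.508.
- False negatives avoided, not counted, 19 × (1 − sens_clin) × sens_dig: from 19 × 0.20 × 0.90 = 3.42 to 19 × 0.30 × 0.95 = 5.42.

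**Net reading, per 1,000**

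- Examinations avoided, 990 × (spec_dig − spec_clin): 990 × (0.90 − 0.95) = −49.5 to 990 × (0.90 − 0.99) = −89.1. At equal specificities it is 0; at 98% against 97% it is +9.9.
- Extra missed cases, 10 × (sens_clin − sens_dig): 10 × (0.80 − 0.90) = −1.0 to 10 × (0.70 − 0.95) = −2.5.

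**What the sign then says.** Let K be a positive cost difference.

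- First ratio: digital dearer by K with 50 more unnecessary examinations gives K/(−50). Digital cheaper by K with 50 fewer gives (−K)/50. The values are equal, with opposite conclusions.
- Second ratio: dearer by K with 2 more missed cases gives K/2. Cheaper by K with 2 fewer gives (−K)/(−2). Again they are equal.

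**Illustrations under assumed inputs**

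- Digital specificity uniform on 90–99% and clinical on 95–99%: the net number avoided is negative with probability 1 − (4/9 × 1/2) = 7/9, about 78%. The simulated 95% range is −76 to +26 per 1,000.
- Sensitivities drawn as independent Beta(19p + 0.5, 19(1 − p) + 0.5): the chance that digital screening misses more is 2% (95% v 70%), 4% (95% v 75%), 8% (95% v 80%), 11% (90% v 75%) and 20% (90% v 80%). The 95% interval of the difference includes zero in all but the first. With 17 against 14 of 19 detected, the chance is about 10%.

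**The case against.** The strongest reply is that the section defines its outcomes explicitly and that, as defined, neither can be negative. This is correct. A reader might infer from the specificity figures that the denominators must be negative; the documents do not support that. It follows only on the net reading, and for examinations avoided it is certain only at the 90% floor, not at the higher specificity hoped for.

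A reader might also infer that the simulation cannot tell a better strategy from a worse one. That too goes beyond the text: the simulation is to give costs and outcomes for each strategy, so the quadrant of every draw can be recovered. Only the ratio summary hides it. A plane, a curve and a rule for dominance could also stand in a fuller document, and their absence from an article is no fault.

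Finally, the Discussion calls the classifier complementary to existing screening. If it were applied only to clinically positive newborns, the two defined counts would be its whole effect. But that use could not raise sensitivity, which the Discussion names as a goal, and Aim 3 compares digital with clinical screening as two strategies.

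What remains is not missing detail. The article fixes the primary outcome and the definitions, and they do not fit together.

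**Conclusion.** The point holds as a mismatch in a stated rule. On the literal reading, at the 90% floor, about 9 to 45 examinations per 1,000 are credited while 94 to 98 new false positives are ignored, so a strategy with a net excess of unnecessary examinations would show a positive number avoided. The 3.4 to 5.4 false negatives avoided among 19 cases are ignored too, and the missed-case count has a 20–51% chance of being zero. On the net reading, examinations avoided are −50 to −89 per 1,000 at the floor and of either sign above it. Extra missed cases are −1.0 to −2.5 per 1,000. In neither ratio does the sign separate cheaper-and-better from dearer-and-worse.

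The net figures rest on the protocol's performance values and on 1% prevalence in the low-risk group. The literal counts also need conditional independence, and those for SHD need 19 cases. The 78% and 10% are illustrations, not predictions. This is a cheap improvement.

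**What to change.** 1. Define both outcomes as net differences between strategies, counting all discordant cells: false positives per 1,000 and missed SHD cases per 1,000. Report each with an interval that respects the pairing, since every newborn has both screens.
2. Replace the two ratios as primary summary with incremental net monetary benefit (value per SHD case detected × additional cases detected − incremental cost), over a stated range of values. Unnecessary examinations enter through their cost. Costs of missed diagnoses are already a model input, so the value per detected case should not count them again.
3. Show the planned Monte Carlo draws on a cost-effectiveness plane and an acceptability curve.
4. Keep any incremental cost per additional SHD case detected as secondary, reported only with the share of draws in each quadrant, because that denominator can also cross zero.

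The model and the draws stay the same, and no newborn is added. The one downside is that a range of values per detected case must be stated. This should be settled before results are seen, so that they cannot steer the choice of reading.
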